#### Instruments and procedures

##### Eligibility evaluation

After clarifications regarding the research and declaration of voluntary participation via the consent form, the participants will answer a social-demographic survey composed of closed questions about age, gender, level of education, socio-economic level, religion, sexual orientation, parents’ professions, parents’ educations, previous dating experience, romantic status (whether single or dating), and how long have they been dating. The participants between 15 and 29 years of age who have a current romantic partner will be included in the intervention, while those who do not meet both criteria will be excluded (Fig. 2).

**Fig. 2 Fig2:**
[figure not shown]
Evaluation flowchart

##### Baseline

The included participants will next respond to the baseline evaluation, which will assess attachment style; conflict resolution skills; victimization and perpetration of psychological, physical, and/or sexual violence in their partners; and relationship quality.

### Attachment

Attachment will be evaluated by the Experience in Close Relationships Scale, short version (ECR-Short). The original scale comprises twelve items and was developed by Wei et al. [49] from the full Experience in Close Relationships Scale, which has 36 items, by Brennan, Clark and Shaver [50]. In Brazil, the adaptation was done by Natividade and Shiramizu [51], and contains 10 items that evaluate two factors: anxiety related to attachment (preoccupation with maintaining the romantic relationship and the partner’s responsiveness and the need for physical and emotional closeness, for example: “I need a lot of assurance that I am loved by my partner”) and avoidance related to attachment (discomfort with emotional proximity, with dependence on a romantic partner, and a preference for emotional detachment, for example: “In general, I try to avoid strong affective closeness with my partner”). Low avoidance and low anxiety indicate secure attachment, while high rates of avoidance and/or anxiety reveal insecure attachment styles. The items are answered on a seven-point Likert scale. Higher scores indicate higher levels of anxiety and avoidance and thus an insecure attachment style.

### Conflict resolution skills

Conflict resolution skills are evaluated through the Conflict Resolution Behavior Questionnaire (CRBQ), developed by Rubenstein and Feldman [52] and adapted to Brazil by Delatorre and Wagner [53]. The instrument is composed of 22 items that evaluate the frequency with which strategies of conflict resolution by avoidance (for example: “I stay cool and distant and don’t pay attention to the other person”), attack (for instance: “I am sarcastic”), and agreement (for instance: “I apologize to the other person”) are employed. A five-point Likert scale is used, ranging from 1 (never) to 5 (always). In the study by Delatorre and Wagner [53], internal consistency levels of 0.68 to 0.79 were found.

### Victimization and perpetration of dating violence

The Conflict in Adolescent Dating Relationship Inventory (CADRI) [54], Brazilian version by Oliveira et al. [1] will be used to evaluate victimization and perpetration of dating violence. In this study, a short version of CADRI will be used. This version is composed of 24 items that evaluate perpetration and victimization various types of violence: psychological (16 items, for instance: “He/she talked to me in a hostile or mean way”); physical (four items, for example: “He/she pushed me or he shook me”); and sexual (4 items, for instance: “I touched him/her sexually when he/she did not want to be”). The participants are requested to indicate the frequency of violent events in the current relationship on a four-point scale (always = it happened six or more times in my current relationship, sometimes = it happened three to five times in my current relationship, rarely = it happened once or twice in my current relationship, never = it has never happened in my current relationship).

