### Efficacy evaluation

#### Objectives

The intervention was designed to reduce victimization and perpetration of physical, sexual, and psychological violence in dating (primary outcomes) and to boost the quality of the romantic relationship as well as conflict management skills and help seeking (secondary outcomes).

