#### Calculation of the sample size

The calculation of the sample size for this study uses a conservative procedure to identify a 10% reduction in dating violence prevalence on the intervention group compared to the control group. Adopting a significance level of 5%, a testing power of 80%, and a 50% dropout rate over the course of the study, it was calculated that each condition should have 610 individuals.

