#### Follow-up

At three months after the end of the intervention, the experimental and control group participants will again respond to measurements of conflict resolution skills, victimization and perpetration of violence, and relationship quality. Additionally, they will also fill out the Seeking Help Questionnaire. This instrument, developed by the authors, is composed of three closed questions that inquire whether the respondents sought any sort of help to deal with their affective relationship since they first entered the research website, whom they asked for help, and what the perceived efficacy of the help received was.

Additionally, the Dating SOS participants will be asked to evaluate the impact of the intervention by responding to the Dating SOS Impact Questionnaire, composed of one closed question (How would you evaluate the effects of Dating SOS in your life?) with a multiple choice answer (e.g.: It helped me to end the violent relationship) and three open questions (If Dating SOS made no difference in your life, what do you attribute this to?; If Dating SOS had some effect in your life, what do you attribute this to?; Comment freely about what you thought of Dating SOS).

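### The primary violence measure counts events over the whole current relationship, so it cannot show a fall in participants who keep the same partner and is insensitive to the planned 10% difference

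*Protocol article*

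**What the plan says.** The protocol article's Objectives section states that the intervention was designed to "reduce victimization and perpetration of physical, sexual, and psychological violence in dating (primary outcomes"). The section on victimization and perpetration assigns these outcomes to a short CADRI with four response options: "The participants are requested to indicate the frequency of violent events in the current relationship on a four-point scale". All four refer to the relationship as a whole: the lowest is "never = it has never happened in my current relationship" and the highest is "always = it happened six or more times in my current relationship". The two middle options, one or two events and three to five events, are anchored in the same way.

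The Follow-up section times the second assessment: "At three months after the end of the intervention", participants "will again respond to measurements of conflict resolution skills, victimization and perpetration of violence, and relationship quality". It gives no different reference period for the violence items. In the same section the help-seeking questionnaire does have a bounded window, counted from the participant's entry to the study website.

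The sample-size section aims to "identify a 10% reduction in dating violence prevalence on the intervention group compared to the control group". The Statistical analysis section plans comparisons within and between groups from baseline to follow-up, using multivariate analysis of covariance with attachment style and violence status as covariates. Everyone has a current partner at entry, and Table 1 lists ending the relationship among the protective action plans of Session 4.

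**The concern.** A count over the whole relationship is cumulative. While the partner stays the same, the true answer at follow-up is the baseline answer plus whatever happened since. Someone who had one event before enrolment can never return to the lowest category, and someone already in the top category stays there even if violence stopped on the first day.

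The trial's stated aim is reduction, and the intervention also serves young people already in violent relationships. For those who stay with their partner, the benefit they most need, that existing violence stops, leaves the score where it was. A working intervention could therefore look weak.

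Partner change adds a second problem. A new relationship restarts the count, the intervention promotes leaving violent relationships, and the article does not say which relationship is rated after a separation. A difference in break-ups between arms could then appear as a difference in violence, with no means of separating the two.

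**Working it through.** **1. The plan's own figure.** The article states 5% significance, 80% power, 50% dropout and 610 per arm. It gives neither the control prevalence nor whether the test is one- or two-sided. Assume 50% vs 40%, a one-sided 5% test and no continuity correction:

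n = [1.645 × √(2 × 0.45 × 0.55) + 0.842 × √(0.50 × 0.50 + 0.40 × 0.60)]² / 0.10² = 305 per arm, and 305 / (1 − 0.5) = 610.

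This reproduces the stated figure. With a two-sided test the same inputs give 388, or 776 after dropout. Whichever derivation was used, 610 less 50% dropout leaves 305 completers per arm, which is used below.

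**2. What the scale can do for a participant with the same partner.** Assuming accurate recall:

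| Baseline category | Violence stops | Violence continues |
|---|---|---|
| Never | Never | Rises |
| 1–2 events | Unchanged | Unchanged or rises |
| 3–5 events | Unchanged | Unchanged or rises |
| 6 or more | Unchanged | Unchanged (cap) |

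No cell shows a fall. The arms can differ by new onset (first row) or by slower upward movement (second and third rows). In the last row, stopping and continuing look the same.

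**3. Effect on prevalence.** Let P be the share with any event at baseline, q the onset among the rest by follow-up (about four months from baseline: four weekly sessions plus three months), and r the factor by which the intervention multiplies onset. For participants with the same partner:

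- control prevalence = P + (1 − P) × q
- intervention prevalence = P + (1 − P) × q × r
- difference = (1 − P) × q × (1 − r)

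The article gives neither P nor q for the current relationship. Its figure of eight in ten is for lifetime experience at ages 15 to 19, so 80% serves only as the upper end of an assumed range. With q = 20%, a two-sided 5% test of two proportions, unadjusted, and 305 per arm:

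| P | r | Control | Intervention | Difference | Power |
|---|---|---|---|---|---|
| 80% | 0.5 | 84% | 82% | 2 points | about 10% |
| 80% | 0 | 84% | 80% | 4 points | about 25% |
| 50% | 0.5 | 60% | 55% | 5 points | about 24% |
| 50% | 0 | 60% | 50% | 10 points | about 70% |
| 30% | 0.5 | 44% | 37% | 7 points | about 42% |
| 30% | 0 | 44% | 30% | 14 points | about 95% |

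**4. Onset needed for a 10-point difference.** Setting the difference to 0.10 gives q = 0.10 / [(1 − P)(1 − r)]. If all onset is prevented, control onset must be 14% (P = 30%), 20% (P = 50%) or 50% (P = 80%). If onset is halved, it must be 29%, 40% or 100%.

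**The case against.** A reader might infer that the trial cannot register any reduction at all. The documents do not support that, for these reasons.

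- **The sizing target is a comparison between arms.** A cumulative count still separates randomised groups if fewer new events accrue in one of them. This stands. What is lost is the fall within participants who keep their partner.
- **Onset is not the only route.** On a four-level scale, participants in the two middle categories can move up more slowly. Stopping is wholly hidden only for items already at the cap, or if the score is reduced to any versus none. This also stands.
- **The planned analysis is not an unadjusted test of two proportions.** The sample-size section speaks of prevalence, but the analysis section plans multivariate analysis of covariance. One simulation used cumulative scores in participants with the same partner, perfect recall, and assumed event rates and relationship lengths. Halving new events gave 95–100% power with adjustment for the full baseline score, 23–39% with only a three-level violence-status covariate, and 8–16% unadjusted. A 20% cut in events gave 26–50% even with full adjustment. So the loss depends on the adjustment and the effect size. The covariate that the article names is violence status.
- **The 80% example is pessimistic.** It is a lifetime figure for any partner in a narrower age group. At 30% baseline prevalence the picture is milder, and this is universal prevention, so averted onset is a legitimate target.
- **Leaving a violent partner can be an intended benefit.** A lower score after a separation is not necessarily spurious. But without a rule for the relationship rated, the data cannot tell safety gained from a count restarted.
- **The follow-up form is not printed, and the article is condensed.** It might carry another window. As published, the same measure is repeated with no change stated.

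**Conclusion.** The point holds in limited form. As written, the primary measure cannot show a decline in participants who keep the same partner, and stopped violence is not recorded as a fall. Differences between arms can come only from fewer new events, diluted by earlier history, or from partner change.

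The measure is therefore insensitive to the planned 10% lower prevalence, most of all where baseline prevalence is high. At 80% baseline prevalence even complete prevention of onset yields 4 points. At 50%, only complete prevention reaches 10.

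These figures assume accurate recall, no change of partner, an any-violence outcome, 20% control onset and no adjustment. Recall error or a new partner could lower reported scores, but neither would be evidence of less violence with the same partner. The conclusion about direction, that the score cannot fall with the same partner, needs only accurate recall and the stated response options. It is worth correcting before baseline data are collected, because no later analysis can recover a period that was never asked about.

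**What to change.** Give the CADRI outcome items a fixed recall window of equal length at baseline and follow-up, for example the last three months, so that the follow-up window lies after the intervention. Define the primary outcomes from that window.

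State which relationship or partner is rated when the participant has separated or changed partner, for example any partner within the window. Keep the wording about the current relationship at baseline, for tailoring the feedback only.

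The cost is a wording change in an online questionnaire, a short amendment and a few extra baseline items. The outcome would be somewhat less directly comparable with earlier CADRI data.

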### Relationship quality

A short version of the instrument *Romantic Relationship Quality Scale*, developed by Murta et al. [55], will be used, with 21 items on a five-point Likert scale (1 = nothing to do with us; 5 = everything to do with us). The scale is composed of two factors. The first is sexual-affective closeness (alpha = 0.87), comprising 12 items (for instance “I’m affectionate with him/her”), which evaluates mutual help and support, appreciation of each other’s company, self-revelation, empathetic listening, respecting the other’s world (including his/her family), and enjoying physical and sexual intimacy with the other person. The second factor is responsiveness (alpha = 0.88), comprising 9 items (for example “I trust him/her”), which evaluate trust in the other person, admiration for the other person, the perception of what the other person likes or feels, commitment to the relationship, and acceptance of the other’s individuality.

#### Follow-up

At three months after the end of the intervention, the experimental and control group participants will again respond to measurements of conflict resolution skills, victimization and perpetration of violence, and relationship quality. Additionally, they will also fill out the Seeking Help Questionnaire. This instrument, developed by the authors, is composed of three closed questions that inquire whether the respondents sought any sort of help to deal with their affective relationship since they first entered the research website, whom they asked for help, and what the perceived efficacy of the help received was.

Additionally, the Dating SOS participants will be asked to evaluate the impact of the intervention by responding to the Dating SOS Impact Questionnaire, composed of one closed question (How would you evaluate the effects of Dating SOS in your life?) with a multiple choice answer (e.g.: It helped me to end the violent relationship) and three open questions (If Dating SOS made no difference in your life, what do you attribute this to?; If Dating SOS had some effect in your life, what do you attribute this to?; Comment freely about what you thought of Dating SOS).

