		Identify models of positive loving relationships: friends, aunts and uncles, cousins, parents, grandparents, stepparents, and neighbors
	Action plans for increasing relationship quality in day-to-day coexistence	Identify damage potential in risky action plans for daily interaction: lack of communication, ignoring the partner’s needs, shutting down and ignoring one’s own needs, and not respecting the partner’s individuality.
		Construct positive action plans for daily interactions: noting the partner’s needs and providing help sensitively, sharing personal needs with the partner, asking for help, and respecting the partner’s individuality.
Session 3	Social norms regarding dating violence	Weaken the acceptance of socially disused gender stereotypes that justify violence.
	Self-efficacy in handling dating conflicts	Recognize the most challenging dating conflict situations to deal with in a non-violent way: cheating, lying, provocation, an attack by one’s partner, a bad temper, being drunk, and repeated violence.
	Action plans for non-violent dating conflicts	Identify the potential for damage in risky action plans for handling conflict: retaliation, resignation, use of alcohol or drugs, withdrawal, empathy (for victimization).
		Construct positive action plans for handing conflict: regulation of emotions, assertiveness, recognizing errors and apologizing, empathy (for perpetration), and ending the relationship.
Session 4	Attitudes toward dating violence	Strengthen the understanding that violence can be detrimental by harming the relationship, the victim, the perpetrator, and future generations.
		Weaken the perception that violence can be advantageous by granting power, self-defense, affectional gains, and financial gains.
	Social support for protecting oneself from dating violence	Recognize sources of social support for protection in the face of relationship violence.
		Actively seek social support and give clear indications that support is needed, as people may be reluctant to be invasive and help.
		Think critically and refuse social support for accepting violent relationships on the basis that they are a source of economic support, wealth, power, or that one should honor the relationship or protect the children.
	Action plans for freeing oneself from dating violence	Construct positive action plans for protecting oneself against violence: separating from the partner, seeking help, and ending the relationship.

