#### Participants and design

An experimental design with a pre-test evaluation and three-month follow-up will be used. Youths between 15 and 29 years of age and their current partners will be invited to participate. A sample of 1220 youths, which will be randomly and evenly divided between the experimental and control groups, is expected. Participants younger than 15 and older than 29 or not currently in a dating relationship will be excluded from the intervention.

The intervention group will receive the SOS Dating intervention, while the control group will receive general information about dating violence, life skills, and sexual and reproductive rights, based on the book “Telling a night out from a trap: a Guide for the Empowerment of Teens in Intimate Relationships” (Diferenciando Baladas de Ciladas: um Guia para o Empoderamento de Adolescentes em Relacionamentos Íntimos) [48], available at http://www.geppsvida.com.br/publicacoes/cartilhas-e-guias/.

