### Statistical analysis

Descriptive statistics will be used to describe the characteristics of the participants in the baseline and usability data. The principal analyses will consist of intra- and intergroup comparisons between the baseline and the three-month follow-up on the outcomes of victimization and perpetration of physical, psychological, and sexual violence; quality of the romantic relationship; and conflict management skills. Multivariate analysis of covariance will be used to examine the efficacy of the intervention on these outcomes. The attachment style and the relationship’s violence status will be used as covariates. In addition to this, intergroup comparisons will be conducted using the *t*-test on the three-month follow-up outcome of seeking help. Moderation analysis will be employed to evaluate the differential effects of the intervention based on gender, age, and sexual orientation. A significance level of 0.05 will be adopted.

Omitted or incomplete data will be handled via multiple imputation using the Missing Value Analysis procedure of SPSS Statistics. Intention-to-treat analyses will be carried out, and all randomized participants will be posteriorly included regardless of having completed the intervention or not. The effects of Dating SOS will be estimated utilizing Cohen’s d (where values around 0.2 = small effect size; around 0.5 = medium effect size; and around 0.8 = large effect size).

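### The follow-up violence and relationship-quality measures refer to a current relationship, yet no rule or partner-status item covers participants whose relationship has ended, so the primary comparison can be biased if separation differs by arm.

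*Protocol article*

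**What the plan says.** Entry requires a current romantic partner (Eligibility evaluation), and romantic status is asked of everyone at that stage.

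Ending the relationship is an intended result for some participants. The Theoretical basis section anticipates it for those exposed to violence. Table 1 lists it among the positive action plans for conflict in Session 3. For Session 4 it gives: "Construct positive action plans for protecting oneself against violence: separating from the partner, seeking help, and ending the relationship".

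The CADRI section says events are counted within the respondent's current relationship. All four response categories, including never, are defined that way, with no option for someone without a partner. The Relationship quality section describes items about the couple and the partner.

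At follow-up, "the experimental and control group participants will again respond to measurements of conflict resolution skills, victimization and perpetration of violence, and relationship quality". Both arms also receive a help-seeking questionnaire. The Dating SOS arm alone receives an impact questionnaire, where one example answer is "It helped me to end the violent relationship".

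Under Statistical analysis, "Omitted or incomplete data will be handled via multiple imputation", and all randomised participants are to be analysed.

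**The concern.** Separation occurs after randomisation, and the intervention encourages it for participants in violent relationships. The outcome scale presupposes that a relationship exists. A participant who has left therefore has no defined score, and the score that results depends on how that person reads the form. A participant with a new partner does produce a score, but it concerns a different, younger relationship whose count starts again, so it cannot be compared with baseline.

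At stake is the between-arm comparison of victimisation and perpetration, the primary outcomes. If more intervention participants separate, the ambiguous scores fall more heavily on one arm. An analysis plan could not repair this later, because it cannot recover partner status, or recent violence by an ex-partner, that was never asked.

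**Working it through.** **The plan's own yardstick.** The design aims to "identify a 10% reduction in dating violence prevalence on the intervention group compared to the control group". The article gives neither the control prevalence nor the sidedness of the test. Assuming 0.50 versus 0.40, one-sided 5%, 80% power and pooled variance:

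n = [1.645 × √(2 × 0.45 × 0.55) + 0.842 × √(0.50 × 0.50 + 0.40 × 0.60)]² / 0.10² = (1.157 + 0.589)² / 0.01 ≈ 305 per arm.

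The stated 50% dropout gives 305 / 0.5 = 610, which matches the stated size. Other assumptions also reach it (0.60 versus 0.50 gives the same number). The sample size is not in question here; it only supplies a scale of about 10 points, if the reduction is absolute.

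**What a participant can record at follow-up**, on the wording in the article:

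- *Same partner.* The count covers the whole relationship, so it cannot truly fall below baseline.
- *Single.* Three responses are possible: blank, which goes to multiple imputation; never; or the history with the ex-partner, which stays positive if it was positive at baseline.
- *New partner.* The count starts again.

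No listed item distinguishes these cases in both arms.

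**Illustration.** None of these rates is in the document:

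- 50% of relationships are violent at baseline in each arm.
- Non-violent relationships end in 15% of cases in both arms.
- Violent relationships end in 20% (control) and 40% (intervention).
- There is no onset and no effect among couples who stay together, which isolates the separation route.

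Violent and continuing: control 0.5 × 0.80 = 0.40; intervention 0.5 × 0.60 = 0.30.
Violent and ended: 0.5 × 0.20 = 0.10; 0.5 × 0.40 = 0.20.
Non-violent and ended: 0.5 × 0.15 = 0.075 in each arm.
All leavers: 17.5% and 27.5%.

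| Response of leavers | Control | Intervention | Difference (points) |
|---|---|---|---|
| All answer never | 0.40 | 0.30 | 10 |
| All blank, imputed from baseline violence status | 0.40 + 0.10 = 0.50 | 0.30 + 0.20 = 0.50 | 0 |
| All rate the ex-partner | 0.50 | 0.50 | 0 |

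For reference, restricting to continuing couples would give 0.40 / 0.825 = 48.5% and 0.30 / 0.725 = 41.4%, a gap of 7.1 points. That is not the planned analysis.

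With 20% versus 30% of violent relationships ending, the table's differences become 5, 0 and 0 points. With equal rates they are all 0.

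**Direction.** Let f be the share of participants who left a violent relationship but still suffer or commit violence with the ex-partner. The true difference in recent violence is then 0.5 × (0.40 − 0.20) × (1 − f), or 10 × (1 − f) points. At f = 0 it is 10: answers of never are right, while imputation or rating the ex-partner loses the whole effect. At f = 1 it is 0: answers of never create a 10-point benefit that does not exist. At f = 0.5 it is 5, and the table misses it on one side or the other.

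**The case against.** The strongest reply is that the article condenses a fuller protocol. It describes the CADRI wording once, within the baseline battery, and does not reproduce the follow-up form. The form may carry a status question, and rules for separation may sit in the full protocol or analysis plan. This is fair, and if both arms are already asked about partner status, part of the point falls away. What remains is that the article says participants respond again to the same measures, lists what is added at follow-up, and states a general imputation rule with no exception.

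The figures are also open to challenge. Every rate is assumed, and the zero under imputation follows from assuming no effect in continuing couples and imputing from baseline status. That is correct; they show dependence on an unstated rule and do not estimate this trial's bias.

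Several stronger readings are tempting but unsupported:

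- *That the intervention's main benefit is lost.* The article describes universal prevention with several routes, including awareness, attitudes, norms, self-efficacy and conflict management. Leaving is one route, for those exposed to violence.
- *That leavers will be imputed as though still together.* This happens only if they leave the items blank, and nothing in the article says they will.
- *That the plan estimates the effect only in surviving relationships.* The commitment to analyse all randomised participants says otherwise.
- *That every outcome is affected alike.* The conflict-resolution items are not shown to be tied to a current relationship, and help seeking has its own time frame.

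**Conclusion.** The point holds as a defect in outcome definition and data collection. For participants who are single at follow-up the violence and relationship-quality scores are undefined; for those with a new partner they exist but are not comparable with baseline. The planned data cannot identify either group in both arms, nor compare separation between arms.

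Bias in the arm comparison is conditional: it arises if the intervention changes the rate of separation, as it intends for violent relationships, and its direction depends on how leavers respond and whether violence continues after separation. Under the assumed 20% versus 40%, the recorded difference runs from 0 to 10 points across the three uniform responses, as large as the design effect if that is absolute. These are prevalence figures, whereas the planned multivariate analysis is described on the outcome measures, so they show the mechanism only. The matter should be settled before follow-up data are collected.

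**What to change.** At follow-up, ask both arms whether the baseline relationship continues, when it ended if not, and whether there is a new partner.

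Introduce a fixed CADRI recall window, for example the three months before follow-up, covering any partner or ex-partner. The help-seeking questionnaire already uses a defined period, so this is not foreign to the design. Score participants with no violence in the window as zero rather than missing; score violence by or against an ex-partner as reported. Do not impute violence scores as if the relationship had continued.

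Analyse relationship quality among partnered participants, labelled as a subset formed after randomisation, and report separation by arm.

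The cost is a few closed items in an online form and some analysis wording, with no extra participants. The downside is that follow-up wording will differ from the baseline CADRI unless the same window is also used at baseline.
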